### Healthcare System Outcomes

Measures of youth mental healthcare system utilization will be compared between the intervention and wait list control participants. Independent t-tests will compare the number of system contacts, number of service delivery visits and length of service delivery visits for each timeframe (with/without intervention access). Chi-square statistics will compare categorical variables (type of system contacts, type of service delivery visit, professional seen, purpose of service delivery visit) between the intervention and control participants for each timeframe. Linear regression models will compare these outcomes between the intervention and control participants, adjusting for demographic variables (age, sex, mental health concern). Repeated measures models will evaluate the pattern of changes to mental health service use throughout study participation.

The frequency of lifestyle support during mental health services will be evaluated using mixed methods. Each comment in the research database will be coded to indicate the focus (assessment, discussion, recommendation), content and information conveyed by the comment utilizing the same procedures and coding framework developed during our retrospective chart review^44^. Descriptive statistics (frequency tabulations, means or medians (variance) as appropriate) are then used to summarize the data. We will also analyze these data qualitatively, using an inductive approach (no preconceived coding framework). Independent analyses of the qualitative data will be completed by two members of the research team to summarize the lifestyle-related discussions during patient visits. Inductive analyses will begin with data immersion, reading/re-reading the extracted comments. Analytical notes and key phrase identification will identify concepts and enable initial code creation (NVivo nodes). Analyses, interpretation and revisions will continue throughout the analytical process. Data will be interpreted relative to understanding lifestyle needs and counselling for these youth. Key findings will be reviewed separately by age group (12-14, 15-17), sex and type of treatment to identify any trends suggesting that lifestyle needs vary systematically.

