### Research Questions

1. Do youth (12 to 17 years of age) who engage in the 6-month HELP e-intervention have a larger improvement in emotional health (measured by the Strengths and Difficulties Questionnaire) than youth who do not receive the intervention?
2. Does engagement in the HELP e-intervention improve lifestyle behaviour (physical activity, sleep or screen time)?
3. Are changes in emotional health and lifestyle behaviours sustained for at least 6 months after completion of the HELP e-intervention?
4. Do youth who engage in the 6-month HELP e-intervention utilize fewer mental healthcare resources, during and for 1 year following RCT participation, than youth who do not receive the intervention?
5. Do mental health professionals supporting youth who engage in the 6-month HELP e-intervention provide lifestyle behaviour support less frequently than for youth who do not receive the intervention?
6. Are self-reported (i.e., perceived) lifestyle behaviour changes (study questionnaire responses) aligned with objective measures of screen time (smartphone tracking) and sleep and physical activity (accelerometry) in a randomly selected sub-sample (1 of 3) enrolled participants?

We hypothesize that youth engaging in the HELP e-intervention will have improved emotional health and enhanced lifestyle behaviours in comparison to those receiving the delayed (post 6-months) intervention. We hypothesize that changes during the intervention will be maintained for an additional 6 months, and that self-reported measures will accurately reflect objective measurements. We hypothesize that youth engaging in the HELP e-intervention will require fewer youth mental health supports, and when supported will be less likely to require treatment directed at lifestyle behaviours.

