## Expected Duration of Participation

Youth will participate in the study for 12 months. All study visits and assessments are completed remotely. Youth can choose to complete the assessments via RedCAP survey or to have paper copies of the questionnaires sent by mail. The research coordinator will work virtually with each participant to support questionnaire completion. Completion of all questionnaires will require approximately 1 hour at each assessment timepoint. One of every three participants will be randomly selected to complete the objective behaviour measurements in addition to the questionnaires. Accelerometers will be distributed and collected by mail so that in-person visits to CHEO are not required. Participants selected for the objective measures will be required to wear an accelerometer on an elastic waistband 24 hours per day for 7 consecutive days. They will also be required to submit a screen shot of their social media screen time (app that already exists in smartphones) daily for the same 7 days. After the four assessment timepoints have been completed, youth will no longer be required to perform study activities but data collection on healthcare system impacts will continue to be collected via medical chart review for an additional 6 months. Participants randomized to the wait list control group will have access to the HELP e-intervention between the 6 and 12-month assessment timepoints.

| **Study Group** | **0 mos** | **0 to 3 mos** | **3 mos** | **3 to 6 mos** | **6 mos** | **6 to 12 mos** | **12 mos** | **12 to 18 mos** |
| --- | --- | --- | --- | --- | --- | --- | --- | --- |
| Intervention | Assess | HELP | Assess | HELP | Assess | ----- | Assess | Medical chart |
| Wait List Control | Assess | ----- | Assess | ----- | Assess | HELP | Assess | Medical chart |

Assess = completion of study questionnaires and objective measures (if applicable)
HELP = access to the HELP e-intervention with kinesiologist support
Medical chart = evaluation of mental health service use and inclusion of lifestyle behaviours in mental health service supports via medical chart review for 18 months from study enrollment

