The research coordinator will collect the healthcare system impact outcomes via medical chart review after participants have completed the 12-month assessment. For the 18 months after study enrollment, we will record the number and type of youth mental healthcare system contacts (request for support, appointment scheduling, treatment visit). We will also track the number, type (e.g., community provider, peer support, outpatient, day treatment, inpatient), purpose (assessment, counselling), professional seen (e.g., psychiatrist, psychologist, social worker, nurse) and length (visit length in minutes) information for each service delivery visit (i.e., appointments/visits with any type of mental healthcare service provider). Health record notes for all mental healthcare visits will be reviewed in detail to identify all content related to sleep, physical activity or screen time assessments, discussions or recommendations for change. The complete text of each lifestyle-related clinic note will be de-identified for any patient-specific information before being transferred to our research database. Sex and mental health diagnoses will also be extracted from health records.

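### Chi-square tests on per-visit attributes name no unit of analysis and would be too liberal if visits are pooled; research question 4 also has no untreated comparator after month 6

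*Protocol*

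**What the plan says.** Under Study Assessments, the chart review captures the type, purpose, professional and length of care "for each service delivery visit (i.e., appointments/visits with any type of mental healthcare service provider"). It covers 18 months from enrolment.

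Under Healthcare System Outcomes, three kinds of comparison between arms are fixed:

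- "Independent t-tests will compare the number of system contacts, number of service delivery visits and length of service delivery visits for each timeframe".
- "Chi-square statistics will compare categorical variables (type of system contacts, type of service delivery visit, professional seen, purpose of service delivery visit"), again for each timeframe.
- Linear regression of these outcomes, adjusted for age, sex and mental health concern.

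The section then adds: "Repeated measures models will evaluate the pattern of changes to mental health service use throughout study participation". Timeframes are described only by access: "for each timeframe (with/without intervention access").

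Research question 4 asks whether HELP youth use fewer mental healthcare resources "during and for 1 year following RCT participation, than youth who do not receive the intervention". Expected Duration of Participation states: "Participants randomized to the wait list control group will have access to the HELP e-intervention between the 6 and 12-month assessment timepoints". The HELP E-Intervention section confirms that every participant is offered access, at once or after six months.

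**The concern.** There are two separate problems.

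**Unit of analysis.** A Pearson chi-square test needs independent records. A youth with several visits has no single professional seen or visit type, so the most natural way to run the named test is to cross-tabulate visits by arm. Visits by one youth tend to share a provider and a programme. Treating them as independent understates the variance, and differences in the mix of services would be declared too often. Visit length carries the same risk if visits are pooled. It is also undefined for a youth with no visits, and HELP is hypothesised to reduce service use. Comparing mean length among attenders therefore conditions on something the intervention is meant to change.

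**Comparator.** Question 4 needs a group without HELP over the whole period it names. After month 6 the design has none. A later arm difference reported as HELP versus no HELP would be mislabelled, and a small or null one could be misread as no effect on healthcare use.

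**Working it through.** **Inputs.** The protocol gives no figure for the healthcare-use tests, so there is no stated result to reproduce. Its only sample size, 122 youth with complete data, belongs to the Strengths and Difficulties Questionnaire. It is used here only to set the scale: 61 per arm, assuming 1:1 allocation, which is not stated. The significance level is 0.05 (Data Analyses). Visits per youth (m) and within-youth correlation (ρ) are not given, so both are assumed over a range.

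**Step 1: formula.** With m visits per youth, the variance is inflated by DE = 1 + (m − 1)ρ. For a table of two arms by three categories (2 degrees of freedom), the actual size of a nominal 5% test is P(χ²₂ > 5.991/DE) = 0.05^(1/DE). Example: m = 6 and ρ = 0.3 give DE = 1 + 5 × 0.3 = 2.5, and 0.05^(1/2.5) = 0.30.

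**Step 2: simulation.** No true arm difference, category shares 0.5/0.3/0.2, Dirichlet-multinomial correlation within youth, 61 youth per arm, 2,000 runs per setting.

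| m | ρ | DE | Formula | Simulated, equal m | Simulated, unequal m (mean as shown) |
|---|---|---|---|---|---|
| 3 | 0.1 | 1.2 | 8% | 9% | 12% |
| 3 | 0.3 | 1.6 | 15% | 15% | 26% |
| 3 | 0.5 | 2.0 | 22% | 22% | 38% |
| 6 | 0.1 | 1.5 | 14% | 13% | 24% |
| 6 | 0.3 | 2.5 | 30% | 31% | 46% |
| 6 | 0.5 | 3.5 | 42% | 46% | 60% |
| 10 | 0.1 | 1.9 | 21% | 21% | 31% |
| 10 | 0.3 | 3.7 | 45% | 45% | 63% |
| 10 | 0.5 | 5.5 | 58% | 60% | 72% |

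With one record per youth, or with ρ = 0, the simulated rate is about 5%. For a two-category variable (1 degree of freedom) the formula gives 7% (m = 3, ρ = 0.1) to 40% (m = 10, ρ = 0.5).

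**Step 3: which outcomes are exposed.** Numbers of contacts and of visits are one value per youth in a timeframe, so no clustering arises. Visit length is exposed only if visits are pooled rather than summarised per youth.

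**Step 4: comparator by period.**

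| Months | Immediate arm | Wait-list arm | Contrast |
|---|---|---|---|
| 0–6 | HELP | None | HELP versus none |
| 6–12 | Access ended | HELP | Earlier versus current access |
| 12–18 | Access ended | Access ended | Immediate versus delayed access |

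An untreated comparator exists for 6 of the 18 months.

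**Step 5: what this does to an effect.** Let E be the effect of HELP on use per six-month period.

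- *The effect persists after access.* Over 18 months the arms differ by 3E − 2E = E, against 3E versus truly untreated youth, which is one third. In months 6–18 alone the difference is 2E − 2E = 0, against 2E.
- *The effect lasts only during access.* Over 18 months the difference is E − E = 0, against E. In months 6–18 alone it is 0 − E = −E, so the sign reverses.

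**The case against.** The strongest reply is that the protocol never says visits will be pooled. It speaks of comparing participants, its regression covariates are youth-level, and recording data per visit does not by itself fix the unit of analysis. A per-youth summary could be set out in a statistical analysis plan. This stands: the inflation is conditional and its size cannot be fixed from the document. It does not remove the point, because the protocol does fix the test, and that test cannot be applied to a youth with several visit types without a summary that is not named. The repeated measures models concern the pattern of use over time and are not said to replace the chi-square tests. Linear regression does not suit nominal categories.

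On the comparator, the delayed access is openly described in the objectives, the hypotheses and the design. The analysis section calls the controls a wait-list group and does not call them untreated. That also stands: the conflict lies in question 4 read against the design. Yet the with/without labels do not resolve it. They do not say which calendar periods are paired, whether the immediate arm counts as without access in months 6–12, or how months 12–18 are classed.

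A reader might infer that claims of fewer contacts or visits are inflated too. They are not, since those counts are per youth. A reader might also object to t-tests on counts as skewed and zero-heavy; the protocol gives no distribution, so that is not part of this point.

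**Conclusion.** Both parts hold in limited form, and both concern non-primary outcomes.

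The chi-square tests on per-visit attributes are specified without a unit of analysis. If visits are pooled, false-positive rates of about 9% to 60% follow for a three-category variable with equal visit counts. This rests on the assumed 3 to 10 visits per youth, correlation of 0.1 to 0.5 and 61 youth per arm. With unequal visit counts the same settings give 12% to 72%. With one value per youth the rate is about 5%. Visit length shares the problem if pooled, and in any case describes attenders only.

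Question 4's comparator does not exist after month 6. The months 0–6 contrast remains a valid randomised comparison of HELP with no HELP. A reader might infer that the missing comparator also produces false positives. The documents do not support that: in the illustration a beneficial effect is diluted, cancelled or reversed, and if there is no effect none is created.

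**What to change.** - State that the youth is the unit of analysis for contact type, visit type, professional, purpose and visit length.
- For the categorical outcomes, compare per-youth use of each type between arms, or fit GEE or mixed models clustered on youth.
- Replace visit length with total visit minutes per youth in each timeframe, counting zero for youth with no visits.
- Define the timeframes by calendar period. Confine the HELP-versus-no-HELP claim to months 0–6 and label months 6–18 as immediate versus delayed access.
- Reword research question 4 to match.

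The cost is slightly more analysis and a narrower claim at 18 months. The data already planned are sufficient.

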## Study Objectives

This study will evaluate the efficacy of 6 months of HELP e-intervention access with kinesiologist support in a randomized controlled trial to determine if the changes in emotional health (primary outcome) and lifestyle behaviours (secondary outcomes) differ from changes among youth with delayed intervention access (control condition). Sustainability of the intervention will be assessed for an additional 6 months. Participants will be youth 12-17 years of age who contact youth mental health services (1Call1Click). We will also evaluate the impact of the HELP e-intervention on the use of mental healthcare services, the need for mental health professional support of lifestyle behaviours and the association between self-reported and objectively measured lifestyle behaviours.

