# Eligibility Criteria

## Inclusion Criteria

Participants will be eligible for this study if they are 12-17 years of age when they are seeking, waiting for or receiving support for emotional distress. To be included in the study, youth must be: a) able to provide informed consent to study participation, b) able to engage in the HELP e-intervention in English (French translation of the e-modules will not be available until intervention efficacy is established), c) willing to be randomized to a study group, d) willing to complete objective behaviour measures if selected (1 of 3 participants), e) willing to complete the study questionnaires, and f) willing to provide consent for evaluation of mental healthcare system outcomes via their health record.

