## Study Procedures/Evaluations

### Recruitment

The primary avenue for recruitment will be via 1Call1Click. During our pilot study of the HELP e-intervention (REB #21 85X) we developed a best practice advisory flag within EPIC (Appendix A) that was provided to 1Call1Click intake staff if the youth met the age criteria for the research study. Youth who access 1Call1Click have an initial assessment by intake staff. Staff have information about the research study and have been educated regarding the inclusion/exclusion criteria. If the research study could be appropriate for the patient, the intake staff will ask the patient/family if they would like more information about research. If the response is positive, intake staff will send an EPIC inbasket message to the research team who will follow up with the patient/family to discuss the study details.

During the pilot study we also received feedback from youth, families and clinicians requesting that the HELP e-intervention be more widely available to youth who are at various stages in their journey to mental wellness. Therefore, additional youth may be recruited through our two secondary recruitment options. CHEO mental health clinicians will be able to refer youth for enrollment in the research study if they have obtained permission from the youth to do so. This avenue for recruitment will enable youth on the wait list for specialist support or who are currently receiving CHEO support to be eligible for study recruitment. We will also distribute the study information via posters (Appendix B) and social media posts (Appendix C) in CHEO patient areas and through our youth partner groups (CHEO Youth Forum, CHEO-RI Family Leader Program, YouthNet / R$é$seau Ado, the study’s Lived Experience Advisory Group, etc.). Youth who contact the research team after viewing the study information will also be eligible to enroll.

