### Study Assessments

A researcher blinded to study group allocation will work with enrolled youth to complete all study assessments. The accurate/reliable study questionnaires include measures of emotional strength (Strengths and Difficulties Questionnaire)^34^, lifestyle choices (Youth Quality of Life-short form)^35^, readiness for behaviour change (Stages of Change Questionnaire^36^), and sleep (Adolescent Sleep Hygiene Scale)^37^, physical activity (Habitual Activity Estimation Scale)^38^, and leisure screen time (Adolescent Sedentary Activity Questionnaire)^39^ behaviours. All enrolled youth will complete all questionnaires at 0, 3, 6 and 12 months. As in our pilot study (REB #21 85X), the questionnaires (Appendix E) will be completed virtually using RedCAP, with automated scoring of the responses according to published methods. At each assessment, youth will be asked to voluntarily self-report age (years), gender (boy, girl, unkown, other, prefer not to answer), and their use of other mental health therapies (Appendix F). Study enrollment does not restrict access to or use of other mental health supports.

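### The healthcare-use regressions omit care status at entry, which costs precision on research question 4; separately, the Study Objectives describe a narrower population than the eligibility criteria admit.

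*Protocol*

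**What the plan says.** **Population.** Study Objectives: "Participants will be youth 12-17 years of age who contact youth mental health services (1Call1Click"). Inclusion Criteria: youth are eligible "when they are seeking, waiting for or receiving support for emotional distress". Recruitment names 1Call1Click as the main route and adds two others. Clinician referral is meant to "enable youth on the wait list for specialist support or who are currently receiving CHEO support to be eligible for study recruitment". For posters and social media, "Youth who contact the research team after viewing the study information will also be eligible to enroll".

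**Question.** Research question 4 asks whether HELP youth "utilize fewer mental healthcare resources, during and for 1 year following RCT participation", compared with youth who do not receive the intervention.

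**Analysis.** Healthcare System Outcomes plans three kinds of comparison for contacts, visits and visit length:
- independent t-tests without covariates (chi-square tests for the categorical items);
- linear regressions "adjusting for demographic variables (age, sex, mental health concern");
- repeated measures models with no covariates named.

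**Available data.** Study Assessments has youth voluntarily report at each assessment, including month 0, "their use of other mental health therapies (Appendix F"). Chart data on service use run for 18 months from enrolment; no collection of earlier use is specified.

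**The concern.** The two population statements do not match. A reader who relies on the objectives would attribute the results to youth at the point of calling 1Call1Click, although some of the sample may have been waiting or in treatment already.

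The analysis point is separate. A youth in treatment at enrolment can be expected to accrue visits from the start, while one who has just called may wait; the protocol's own background cites waits of 8-30 months. If enrolled youth differ in this way, the difference between them goes into the error term of every planned between-arm test of service use. No other listed covariate clearly stands in for it. The efficacy models adjust for support referral, but that is what intake staff recommended, not whether the youth was already in care, and it is not carried into the healthcare-use list. At stake is power for research question 4, a non-primary question.

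**Working it through.** **1. The plan's own figure.** No sample size or power is stated for healthcare use. The stated 122 complete cases concern a 3.4-point SDQ difference at 80% power, with no SD given. Assuming 1:1 allocation and two-sided 5%, the implied SD is 3.4 / [(1.96 + 0.84) × √(2/61)] = 6.7. This says nothing about visits; it is used here only to set 61 per arm.

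**2. General form.** Let R² be the share of variance in service use that entry status explains beyond the planned covariates. The minimum detectable difference at 80% power is 0.507 × √(1 − R²) SD.

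| Assumed R² | Detectable difference (SD) | Power for 0.507 SD |
|---|---|---|
| 0 | 0.507 | 80% |
| 0.05 | 0.494 | 82% |
| 0.10 | 0.481 | 84% |
| 0.20 | 0.454 | 88% |
| 0.30 | 0.424 | 92% |

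**3. Illustration with visit counts (all assumed).** Youth not in care have a mean of m₀ = 3 visits per 6 months. A share p is in care, with mean m₁ equal to 2-4 times m₀. Counts are negative binomial with variance m + m²/k, where k is 1 or 2. HELP multiplies both means by 0.7.

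For each arm:
- within-status variance = (1 − p)(m₀ + m₀²/k) + p(m₁ + m₁²/k)
- between-status variance = p(1 − p)(m₁ − m₀)²

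Let W and B be the sums of these over the two arms. Adjustment removes about B/(W + B) of the variance of the arm difference.

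Central case, p = 0.35 and three times the visits (means 3 and 9; with HELP 2.1 and 6.3):
- B = 0.2275 × 6² + 0.2275 × 4.2² = 8.19 + 4.01 = 12.20
- k = 1: W = 39.30 + 20.33 = 59.63; cut = 12.20/71.83 = 17%
- k = 2: W = 22.20 + 11.95 = 34.15; cut = 12.20/46.35 = 26%

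A simulation of 4,000 trials per setting gave 17.7% and 26.7%, with power rising from 29% to 33% (k = 1) and from 43% to 54% (k = 2). Over p = 20-50% and ratios of 2-4, the simulated cut ran from 6% to 35%.

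Low case, twice the visits (means 3 and 6; with HELP 2.1 and 4.2):
- p = 0.05, k = 1: B = 0.0475 × (3² + 2.1²) = 0.64; W = 13.50 + 7.28 = 20.78; cut = 0.64/21.42 = 3%
- p = 0.10, k = 2: B = 0.09 × 13.41 = 1.21; W = 9.15 + 5.18 = 14.33; cut = 1.21/15.54 = 8%

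**4. Chance imbalance, central case.** The in-care share in one arm has SD √(0.35 × 0.65/61) = 0.061. The resulting shift in the arm difference has SD 0.061 × √(6² + 4.2²) = 0.45 visits. Mean visits without HELP are 0.65 × 3 + 0.35 × 9 = 5.1, so a 30% reduction is 1.53 visits, and the shift is 0.45/1.53 = 29% of it. This is not an extra harm: 0.45² = 0.20 = B/61, the same variance term as in step 3.

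**The case against.** **Validity.** A reader might infer that omitting entry status biases the comparison. It does not: under randomisation the arm difference is unbiased in expectation with or without the covariate.

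**Link between the two points.** A reader might also infer that the healthcare-use analysis was built for the narrow population. Nothing shows this; age, sex and mental health concern are not specific to 1Call1Click callers. The objectives may simply be shorthand for the main recruitment route, and the sample size section also counts direct contacts with the research team. The wording mismatch therefore stands only as a wording matter.

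**Left to a later plan.** Covariate refinement often belongs in an analysis plan, and the repeated measures models leave room for it. That holds for those models, but the regression list is already fixed in the protocol.

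**Size.** The in-care share is assumed. It could be small, since most youth are expected through 1Call1Click. The illustration compares an arm-only model with arm plus entry status, whereas the planned regression already contains three covariates; any overlap between mental health concern and care status lowers the gain. The 61 per arm comes from the SDQ calculation, while service use comes from charts and 100-200 youth are expected to enrol. These points stand. So does the observation that central-case power after adjustment is still only 33-54%, so entry status is not the main limit on this question.

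**A stronger contrast.** It is tempting to set a chance shift of about half a visit against the 0.9-visit effect in youth not in care (30% of 3). The shift arises in the mixed sample, so the mixed-sample effect of about 1.5 visits is the right comparator.

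**Data.** The month-0 therapy report is voluntary, and recruitment route does not determine status. A three-level seeking, waiting or receiving variable is not shown to be collected.

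**Conclusion.** Two modest points hold. The Study Objectives are narrower than the Inclusion Criteria and Recruitment sections and should be aligned with them. The fixed healthcare-use analyses leave out care status at entry, which costs precision, not validity, for research question 4. That entry status predicts visits strongly is plausible but not documented.

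The gain from adjustment cannot be derived from the protocol. Under the assumed visit counts it is roughly a 6-35% cut in the variance of the arm difference if 20-50% are in care with 2-4 times the visits. It is about 3-8% if 5-10% are in care with twice the visits, and smaller again where mental health concern already carries part of the information. The change is worth making because it costs little, not because the planned comparison is wrong.

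**What to change.** **Study Objectives:** restate the population to match the Inclusion Criteria and Recruitment sections, so that conclusions cover youth seeking, waiting for or receiving support.

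**Healthcare System Outcomes:** add month-0 care status to the between-arm regressions of contacts, visits and visit length. Define it as receiving other mental health therapy or not, from the month-0 self-report, together with recruitment route. Name these adjusted models as the main between-arm comparison for research question 4 and keep the t-tests as description.

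**Cost:** one or two degrees of freedom and two wording changes. The variable must be fixed from month-0 information only. Because the self-report is voluntary, the text should say how a missing value is handled, for example as its own category.
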